**WHO trial registration data set items**

| **DATA CATEGORY** | **INFORMATION** |
| --- | --- |
| **Primary registry and trial identifying number** | ClinicalTrials.gov NCT06203860 |
| **Date of registration in primary registry** | 11, January 2024 |
| **Secondary identifying numbers** | S-20230015 |
| **Source(s) of monetary or material support** | Odense University Hospital |
| **Primary sponsor** | Odense University Hospital |
| **Contact for public queries** | [name], PhD, [[contact]] [[[contact]](mailto:[contact])] |
| **Contact for scientific queries** | [name], PhD, Cardiovascular Research Unit, Odense University Hospital – Svendborg |
| **Public title** | The Cardio-Metabolic Clinic (ProtecT-2-D) |
| **Scientific title** | Cardiovascular Protection in Patients with Type 2 Diabetes and Established Heart or Vascular Disease - The Cardio-Metabolic Clinic |
| **Countries of recruitment** | Denmark |
| **Health condition(s) or problem(s) studied** | Type 2 Diabetes, Heart disease, Vascular disease, Cardiovascular disease, organizational structure |
| **Intervention(s)** | Active comparator: Cardio-Metabolic Clinic  Placebo comparator: Standard of care |
| **Key inclusion and exclusion criteria** | Ages eligible for study: ≥18 years Sexes eligible for study: both Accepts healthy volunteers: no  Inclusion criteria:  Diagnosed with type 2 diabetes,  Established heart or vascular disease defined as: (1) Atherosclerotic disease (acute or chronic coronary syndrome, stroke, peripheral arterial disease, imaging proved ischemic heart disease),  (2) Heart failure,  (3) Atrial fibrillation,  (4) Valvular heart disease,  (5) Severe hypertension.  Exclusion criteria:  Short life expectancy, another diabetes type, participation in other interfering clinical trials. |
| **Study type** | Interventional Allocation: randomized Intervention model: 2:1 parallel assignment  Masking: no  Primary purpose: prevention |
| **Date of first enrolment** | 01. Jan. 2024. |
| **Target sample size** | 1500 |
| **Recruitment status** | Recruiting |
| **Primary outcome** | The time to the first occurrence of major adverse cardiovascular event (MACE), a composite endpoint consisting of: Cardiovascular death, non-fatal acute myocardial infarction, non-fatal stroke, or hospitalization for heart failure (time frame: 5 years) |

# Background

The number of patients with type 2 diabetes (T2D) has more than tripled during the last twenty-five years and every 20^th^ person in the Danish population is currently living with T2D (1). The risk of developing cardiovascular (CV) disease or premature death is 2-4 times higher in patients with T2D compared with the general population (2). T2D is a systemic disease that is associated with both macro- and microvascular complications, and is often accompanied by other metabolic disorders like hypertension, dyslipidemia, obesity, and metabolic dysfunction-associated steatohepatitis (MASH). A recent American study (3) showed that half of T2D patients suffered from at least three other cardio-renal-metabolic conditions. Furthermore, patients with T2D have an increased risk of developing diabetic cardiomyopathy and heart failure (4).

The STENO-2-Study (5) demonstrated that multifactorial intervention on CV risk factors in patients with T2D significantly reduced mortality (6), and treatment with statins, angiotensin-converting-enzyme (ACE) inhibitors, and anti-glycemic drugs are the cornerstone in the management of patients with T2D (7, 8). Similarly, the prospective RAMP-study with more than 50.000 participants demonstrated a substantial reduction in CV risk (56.6 %), microvascular complications (11.9 %), and mortality (66.1 %) through multifactorial diabetes and risk factor intervention compared to the standard of care (9, 10).

Recently, new medication has emerged in the field of anti-diabetic treatment and has revolutionized the management of CV risk in patients with T2D. Treatment with sodium-glucose co-transporter 2 (SGLT2) inhibitors and glucagon-like peptide 1 (GLP-1) analogs have been a “game changer” in diabetes treatment and have been shown to reduce CV mortality, cardiovascular events and to be very effective in patients with heart failure and reduced kidney function (11-19). Despite these effective medical treatments, patients with T2D still have an increased risk of cardiovascular death and development of heart failure(2). Furthermore, it is well known that many patients with T2D struggle to reach their target goals for blood sugar levels and CV risk factors (20). Traditionally, the healthcare system focuses on single-disease management. Patients with T2D are managed in specialty-focused outpatient clinics resulting in fragmented care, inadequate treatment, higher costs, and worse CV outcome (21, 22). Therefore, there is a desperate need for a more multidisciplinary and thorough assessment of patients with T2D, and a closer collaboration between endocrinologists, nephrologists and cardiologists in the disease management.

We propose establishing a Cardio-Metabolic Clinic, providing comprehensive assessment and specialized care following current diabetes guidelines. The concept of such clinics have previously been emphasized, often involving collaboration between specialists in cardiology and endocrinology, resulting in high costs (21, 23). Additionally, a recent analysis questioned the cost-effectiveness of primary care based cardio-metabolic risk prevention programs (24). Our goal is to develop an affordable and resource-efficient clinic model. This involves implementing a decision-making algorithm to guide patient care, with medical students or nurses providing the daily patient contact under supervision of a cardiologist.
The primary aim of this randomized controlled trial is to investigate whether a Cardio-Metabolic Clinic is superior to the standard of care in reducing cardiovascular morbidity and mortality in patients with type 2 diabetes and established cardiovascular disease.

## Hypothesis

In patients with T2D and cardiovascular disease, a systematic, specialized multidisciplinary approach in a Cardio-Metabolic Clinic, will result in better management of diabetes and reduced cardiovascular morbidity and mortality.

Aim
This prospective, randomized controlled trial is designed to explore the benefits of a systematic, specialized multidisciplinary approach in a Cardio-Metabolic Clinic in patients with T2D and established cardiovascular disease.

Study design
The study is a single-center, open label, prospective, randomized controlled trial examining the efficacy of a specialized, multidisciplinary approach in patients with T2D and established CV disease (CVD) compared with usual care.

# Methods

Study setting
The study will be carried out at the Cardiovascular Research Unit at OUH, Svendborg Hospital, Denmark.

Study population
Patients with T2D and established CVD, referred from general practices or seen in the outpatient clinic of Cardiology or Endocrinology at Svendborg Hospital, will undergo screening for potential inclusion in the study.

Eligibility criteria
Inclusion criteria:

- >18 years.
- Capable of giving written informed consent.
- Established diagnosis of T2D [26].
- Established heart or vascular disease, defined as either:

1. Atherosclerotic disease defined as:
   i) Prior acute coronary syndrome [27].

ii) Chronic coronary syndrome defined as the combination of: Angina pectoris AND coronary atherosclerosis assessed with either coronary CT angiography or myocardial-scintigraphy or coronary angiography AND treatment with statins and/or acetylsalicylic acid [28].
iii) Stroke [29].
iv) Peripheral arterial disease (PAD) defined as: Claudication intermittence in combination with pathological ankle brachial index AND/OR vascular PAD surgery AND/OR ischemic amputation [30]. v) Ischemic heart disease defined by one of the following criteria: a) Myocardial-scintigraphy: >10% reversibility OR b) Coronary CT angiography: Coronary Artery Calcium-score >100.

1. Heart failure (HF): HF with reduced ejection fraction, HF with Mildly reduced ejection fraction, HF with preserved ejection fraction [31].
2. Atrial fibrillation and/or flutter, including paroxysmal, persistent and chronic disease [32].
3. Valvular heart disease (which requires control in outpatient clinic of cardiology), such as aortic valve stenosis, mitral valve insufficiency, and patients with aortic dilatation.
4. Hypertension treated with at least three antihypertensive drugs.

Exclusion criteria:

1. Life expectancy less than 5 years for any reason.
2. Type 1 Diabetes Mellitus [26].
3. Participation in another clinical trial with an investigational product or device that could interfere with the primary and/or secondary endpoints of this study.

## Screening

Participants will be selected from patients with T2D and established CVD, referred from general practices or seen in the outpatient clinic of Cardiology or Endocrinology at Svendborg Hospital between January 2024 and January 2027 (see figure 1). If applicable, by the in- and exclusion criteria, patients will be contacted by a letter and the study staff will inform the patients of the study. If patients are interested in participation, possible dates for a visit will be arranged.

Informed consent procedures
Eligible participants will receive written material (participant information) by a letter in the e-Boks system before the first visit. On the first visit, patients are given oral information regarding the study and informed consent will be obtained before conducting any study-specific procedures.

**Figure 1: Screening and management program in the Cardio-Metabolic Clinic**

[figure not shown]

*Abbreviations: T2D= Type 2 diabetes, CVD= Cardiovascular disease, GP= General practice, CMC= Cardio-Metabolic clinic, CG=Control group, CV= Cardiovascular, ACS= Acute coronary syndrome, HF= Heart failure.*

Baseline visit
All participant data, including detailed medical histories, will be digitally captured in the electronic-Case Report Form (REDCap). The assessments will encompass: Duration and diabetes-related complications, demographic data (gender, age), cardiovascular disease (including heart failure, ischemic heart disease, atrial fibrillation, valve diseases, peripheral arterial disease, stroke), risk factor status (including hypertension, hypercholesterolemia, smoking habits, alcohol consumption, familiar disposition to ischemic disease), and a detailed record of pharmacological treatments including vaccinations.

Verification of diabetes-related complication such as retinopathy, nephropathy, and neuropathy will be conducted via the Danish Adult Diabetes Database.
Physical examination will be executed, including anthropometric measurements (height, weight, and hip/waist ratio), and blood pressure will be measured after a 10-15 minutes rest period. Additionally, evaluations will include an inspection for diabetic foot ulcers and measurement of the ankle/brachial index (ABI). Electrocardiographic monitoring will be performed.

Biochemistry: Blood and urine samples will be collected. Albuminuria will be evaluated from a spot urine sample. Patients with high levels of the biomarker FIB 4 will have a Fibro-scan performed.

Randomization
Participants, which fulfill the inclusion and exclusion criteria, will be randomized to one of the following programs in a ratio of 2:1. Randomization will be performed using the randomization module available in the REDCap system.

1. Cardio-metabolic group (CMC): Specialized multidisciplinary management of T2D in a Cardio-Metabolic Clinic with a focus on the management of cardiovascular risk factors and assessment of all micro- and macrovascular complications.

2. Control group (CG): Standard of care management of T2D. This consists of a collaboration between the general practitioner and/or endocrinology outpatient clinic and/or cardiology outpatient clinic.

## Interventions – the Cardio-Metabolic Clinic

#### Organization in the Cardio-Metabolic clinic

The Cardio-metabolic clinic is based on a low-cost model and is organized in three different layers centered on the patient. The innermost layer consists of medical students or specialized cardio-metabolic nurses, who have the daily contact with the patients in the Cardio-metabolic Clinic. Patient´s medical history and data from the baseline visit are entered into the Electronic Case-Report Form (REDCap). When Patients are randomized to the intervention arm a decision-making algorithm in the REDCap-system will be activated ensuring that patients receive the most optimal and tailored medical treatment according to the latest guidelines and recommendations for diabetes management. The second layer consists of a cardiologist who the medical students or cardio-metabolic nurses will review the patients risk profile and algorithm-recommended treatment with. If the cardiologist needs further counselling for patient management, the third layer will be contacted. The third layer consists of an endocrinologist, a nephrologist and a hepatologist and this multidisciplinary collaboration will ensure the most optimal diabetes management in challenging cases.

#### Interventions in the Cardio-Metabolic clinic:

Participants in the CMC will follow a decision-making treatment algorithm in the REDCap-system. The treatment algorithm is coded in accordance to the most recent guidelines and recommendations for diabetes management and CVD (32). Consequently, there may be modifications over time. Participants will be categorized into various cardiovascular risk groups using the SCORE2-Diabetes (Figure 2) (32) and will receive interventions targeting nine specific areas (Figure 3); dyslipidemia, hypertension, thrombosis prophylaxis, diabetes management, assessment of microvascular complications, evaluation of SGLT2i and/or GLP1-RA, lifestyle modifications, peripheral artery disease, and vaccinations. The CMC intervention is considered complete when a participant is fully titrated to the targeted or highest tolerated dose in all suggested treatment areas. Endpoint assessments will begin once intervention is completed.

[figure not shown]

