**Five year follow-up:**
A journal audit and look-up in the Danish Health Data Authority will be performed to examine the number of clinical events according to the primary and secondary endpoints.

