## Discontinuation:

Participants will be followed for the complete duration of the study regardless of their adherence to the study intervention. Any component of the study intervention may be discontinued at the discretion of either the participant or the study staff due to safety, behavioral or compliance reasons.

Withdrawal of consent: Participant may withdraw consent at any time upon request. Those considering withdrawal should be offered the option of flexible participation, if feasible. If a participant withdraws consent, any data collected before such a withdrawal of consent may still be used for study purposes. Participants who withdraw will be included as intention-to-treat in the statistical analysis once the study ends.

Lost to follow up: If participants fail to attend and complete the three years follow up visit, they will be considered lost to follow-up for the analysis of the secondary outcomes that requires attendance. However, these participants will still be included in the primary and secondary prognostic outcomes.

Timeline
The study started in January 2024, with a four-year inclusion period that will continue until January 2028. After three years, all patients will have a follow-up visit and baseline assessments will be repeated. Clinical events will be assessed at 5- and 10-years follow-up by journal audits and by look-up in the Danish Health Data Authority. Thus, the 5 years follow-up will be approximately in January 2031, and 10 years follow-up in January 2036 (figure 4).

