**Figure 4 - Timeline for the study**

[figure not shown]

Outcomes The primary outcome is the time to the first occurrence of a composite of CV deaths, non-fatal myocardial infarction, non-fatal stroke, and hospitalization for heart failure.

The secondary outcomes are the time to the first occurrence of one of the single components of the primary outcome, and a combination of the single components of the primary outcome to assess the total symptom burden. Additional secondary outcomes will be the assessment of microvascular complications, protocol driven medical changes and a cost-effectiveness analysis of the Cardio Metabolic Clinic. Primary and secondary outcomes and endpoints are shown in the following table:

| **Primary outcomes** | **Primary endpoints** |
| --- | --- |
| To examine whether patients with type 2 Diabetes (T2D) receiving optimal diabetes care in a Cardio-Metabolic Clinic are superior compared to usual care in reducing; incidence of cardiovascular (CV) death, non-fatal acute myocardial infarction (AMI), non-fatal stroke, and hospitalization for heart failure (HF) | Time to the first occurrence of major adverse cardiovascular event (MACE), a composite endpoint consisting of:   - CV death - Non-fatal AMI - Non-fatal stroke - Hospitalization for HF |
| Units of measure: Measured in days. | Time frame: From baseline to 5 years of follow-up (FU). |

| **Secondary outcomes** | **Secondary endpoints** |
| --- | --- |
| To examine whether patients with type 2 Diabetes (T2D) receiving optimal diabetes care in a Cardio-Metabolic Clinic are superior compared to usual care in reducing; incidence of cardiovascular (CV) death, non-fatal acute myocardial infarction (AMI), non-fatal stroke, and hospitalization for heart failure (HF) | Time to the first occurrence of MACE, a composite endpoint consisting of:   - CV death - Non-fatal AMI - Non-fatal stroke - Hospitalization for HF |
| Units of measure: Measured in days. | Time frame: From baseline to 10 years FU. |
| To compare the individual component, CV death, of the primary endpoint in patients receiving optimal diabetes care in a Cardio-Metabolic Clinic versus usual care. | Time to the first occurrence of:   - CV death   (Presumed cardiac condition leading to death. Including: AMI, venous thromboembolic event, malignant arrhythmia, cardiogenic shock, fatal stroke and aorta dissection) |
| Units of measure: Measured in days. | Time frame: From baseline to 5 + 10 years of FU. |

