**Sample size estimation:**
We anticipate a reduction in the primary endpoint of 15 % in patients with T2D assessed in the Cardio-Metabolic Clinic compared to the standard of care care. With a power of 80% and an alpha value of 0.05.
1306 patients are needed. We anticipate a dropout rate around 10-15% and therefore 1500 patients will have to be included in the study.

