**Descriptive statistics**
Flow of participants will be described with a flowchart for group allocation.
Baseline characteristics between the control group/intervention group will be summarized as mean (SD), median (interquartile range) for continuous variables and as counts (percentages) for categorical variables. Differences between the two groups will be compared with a Wilcoxon rank-sum test for continuous variables and Pearsons Chi2/ Fisher's exact test for categorical variables. Missing data will be specified. Study objectives will be analyzed using the intention-to-treat principle.

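### The protocol gives two incompatible start points for counting primary-endpoint events: baseline, or completion of titration, which exists only in the clinic arm

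*Protocol*

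**What the plan says.** Under *Interventions in the Cardio-Metabolic clinic*, the protocol defines the end of the intervention: "The CMC intervention is considered complete when a participant is fully titrated to the targeted or highest tolerated dose in all suggested treatment areas". The next sentence reads "Endpoint assessments will begin once intervention is completed". No maximum duration is given. The control arm receives standard of care and has no corresponding milestone.

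Other sections set a different start:

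- **Outcomes table, primary endpoint:** "Time frame: From baseline to 5 years of follow-up (FU"). The listed secondary endpoints also run from baseline.
- **Descriptive statistics:** "Study objectives will be analyzed using the intention-to-treat principle".
- **Discontinuation:** "Participants will be followed for the complete duration of the study regardless of their adherence to the study intervention".
- **Five year follow-up:** "A journal audit and look-up in the Danish Health Data Authority will be performed to examine the number of clinical events". The ten-year look-up is described in the same way.

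**The concern.** In a randomised comparison of time to first event, both arms need the same time zero, fixed no later than randomisation. Completion of titration fails this test in three ways. It happens after randomisation, it exists in one arm only, and whether and when it is reached depends on tolerance and on staying alive and event-free. The algorithm works through ordered steps (for blood pressure, five drug classes before referral), so completion may take some time in some participants.

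The protocol has no rule for CMC participants who have an event, die, or never finish titration before completion. Whoever programs the primary analysis must choose between the two statements. In an open-label, single-centre trial, one of those choices would favour the clinic by an amount similar to the planned effect.

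**Working it through.** **1. The passages side by side.** The intervention section starts endpoint assessment at a CMC-only milestone. The outcome table starts it at baseline. Intention-to-treat analysis and follow-up regardless of adherence fit only the second. The scheduled assessments do not explain the sentence either. The three-year appointment is handed out at the baseline visit, and the five- and ten-year look-ups are set by calendar. None of them is triggered by completed titration.

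**2. Inputs.** The protocol has no figure of its own to reproduce on this point.

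- From the protocol: 2:1 allocation ("randomized to one of the following programs in a ratio of 2:1") and 1500 participants, hence 1000 CMC and 500 control; five-year horizon; alpha 0.05, taken as two-sided.
- From the protocol, for comparison: "We anticipate a reduction in the primary endpoint of 15 % in patients with T2D". It does not say whether this is relative or absolute; relative is assumed here.
- Assumed: no true effect; constant hazard; five-year risk R = 20%, with 30% as a second value; the same uncounted period d for every CMC participant.

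**3. Reading A: clock at baseline, CMC events before completion not counted, participants kept in the denominator.**

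- Hazard: λ = −ln(1 − R)/5 = −ln(0.80)/5 = 0.0446 per year.
- Share of CMC participants whose event is lost: L = 1 − exp(−λd).
- Apparent CMC risk: R − L. Apparent risk ratio: (R − L)/R.
- Chance of a false claim of benefit, two-proportion test: Φ[(L − 1.96·SE₀)/SE₁], with SE₀ pooled and SE₁ unpooled.

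Example, d = 6 months: L = 1 − exp(−0.0223) = 0.0221. Apparent CMC risk = 0.200 − 0.0221 = 0.1779, ratio 0.89. Pooled risk = (1000 × 0.1779 + 500 × 0.200)/1500 = 0.1853, SE₀ = 0.0213, SE₁ = 0.0216. Then Φ[(0.0221 − 1.96 × 0.0213)/0.0216] = Φ(−0.91) = 0.18.

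| R | d (months) | CMC events lost per 1000 | Apparent risk ratio | False claim of benefit |
|---|---|---|---|---|
| 20% | 0 | 0 | 1.00 | 2.5% |
| 20% | 6 | 22 | 0.89 | 18% |
| 20% | 9 | 33 | 0.84 | 35% |
| 20% | 12 | 44 | 0.78 | 56% |
| 30% | 6 | 35 | 0.88 | 30% |
| 30% | 9 | 52 | 0.83 | 58% |
| 30% | 12 | 69 | 0.77 | 82% |

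A three-month gap at 20% risk gives about 0.94 and 8%.

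**4. Sensitivity to the denominator.** If CMC participants with an early event are also removed from the denominator, the apparent risk is 1 − exp(−λ(5 − d)). At R = 20% this gives ratios of 0.91, 0.86 and 0.82 for 6, 9 and 12 months. As a rate ratio with baseline as the clock, and for assumed five-year risks of 15% to 50%, the same exclusion gives 0.87–0.89 at 6 months and 0.75–0.79 at 12 months. The direction is the same throughout.

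**5. Reading B: clock restarted at completion, CMC only.** With a constant, common hazard the rate ratio is 1.0, so there is no immortal-time bias. What remains is unequal time zeros, a CMC arm restricted to event-free titration completers, and loss of intention-to-treat. The size of that selection cannot be computed from the protocol.

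**The case against.** The strongest reply is that the sentence stands in a description of clinic workflow, while every section that governs endpoints and analysis points to baseline. Events are gathered from journals and national data at five and ten years, so titration cannot postpone their capture. On this view the sentence is stray operational wording, and a competent analyst would count from baseline.

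Much of that stands. A reader might infer that early CMC events will be dropped and that the primary comparison already carries immortal-time bias. The documents do not support that: no passage discards pre-completion events, and the outcome table says otherwise. Immortal time also needs a particular combination, namely a clock kept at baseline with early CMC events uncounted. Restarting the clock produces a different fault.

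The inputs are also open to challenge. Event rate and delay are assumed, and one delay is applied to everyone. Titration is individual, and participants who need no change may complete almost at once. The loss is nearly proportional to the delay over this range (22, 33 and 44 per 1000), so the average delay matters most if it is unrelated to risk. Participants who never complete would lose all their events under Reading A.

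The reply does not remove the contradiction. The sentence is current text, it names endpoint assessment, and it matches none of the scheduled assessments.

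**Conclusion.** The contradiction over time zero is certain. The bias is conditional on the intervention section governing the analysis. In that case, with the clock at baseline, a 20% five-year risk and no true effect, an uncounted period of 6 to 12 months gives an apparent risk ratio of about 0.89 to 0.78. That range spans the planned 15% reduction if it is relative. The chance of a false claim of benefit would be about 18% to 56% instead of 2.5%. These figures rest on constant hazard, a common delay and an assumed event rate, and they show scale only; they do not forecast the trial's result. With the clock restarted for CMC only, the rate ratio is unbiased under constant hazard, but the randomised comparison is still lost. No reading that applies the sentence to the primary endpoint preserves that comparison, so it should be corrected before analysis.

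**What to change.** Delete the sentence that ties the start of endpoint assessment to completion of the intervention. In its place, state that time zero is the date of randomisation in both arms, and that all primary and secondary events are counted from that date whatever the titration status, including events before or without completed titration. Align the outcome table by defining its baseline as that date. If an analysis of participants with completed titration is wanted, label it exploratory.

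The cost is a short protocol amendment. Events come from journals and national health data for all participants, so no extra data collection is needed, and clinical management does not change.
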